# Fecal microbiota transplantation to reduce immune activation in ART-treated people with HIV with low CD4/CD8 ratio: protocol for the single-blind, randomized, placebo-controlled Gutsy study (CIHR/CTN PT038)

**DOI:** 10.1186/s13063-025-09345-0

**Published:** 2025-12-13

**Keywords:** HIV, Gut microbiota, Fecal microbiota transplantation, Antiretroviral therapy, Immune activation, Inflammation, Microbial translocation, Randomized control trial, Gut mucosa

## Abstract

**Background:**

Despite antiretroviral therapy (ART) controlling HIV viral replication, people with HIV (PWH) remain at risk for inflammatory non-AIDS comorbidities. Factors contributing to comorbidities in PWH on ART include spontaneous release of HIV products, CMV co-infection, microbial translocation, and gut dysbiosis, each driving systemic T-cell activation. In addition to ART, novel gut microbiota-modulating therapies could reduce epithelial gut permeability, microbial translocation, and immune activation. Fecal microbiota transplantation (FMT) from healthy volunteer is a promising therapy to counteract dysbiosis, protect from gut barrier damage, and lower systemic immune activation.

**Methods:**

The Gutsy study is a single-blind, randomized, placebo-controlled clinical trial evaluating the effects of FMT in PWH on ART for more than 3 years, with a viral load below 50 copies/mL, a CD4 count above 200 cells/mL, and a CD4/CD8 ratio below 1.0. All participants undergo a bowel cleanse before receiving FMT or placebo capsules. In the treatment group, 10 participants receive a bowel cleanse then two high doses of FMT delivered via 30 to 40 capsules twice, 3 weeks apart. The placebo group of 10 participants receive a bowel cleanse and capsules filled with microcrystalline cellulose for equivalence in weight and color, administered under the same time course. Peripheral blood mononuclear cells (PBMCs) and stool samples are collected at each visit: before bowel cleanse (baseline 1), before the first (baseline 2) and the 2nd (visit 4) FMT/placebo, 6 weeks (visit 5) and 12 weeks (visit 6) after the first FMT/placebo; colon biopsies are obtained at visits 3 and 6 in an optional sub-study. The primary objective is to assess the effect of FMT on plasma markers of gut epithelial permeability. Secondary objectives include microbial translocation, immune activation, and HIV latent reservoir biomarkers.

**Discussion:**

We hypothesize that large-dose FMT in capsules, but not placebo capsules, will increase the abundance of beneficial microbes in the gut of PWH on ART, leading to decreased gut damage markers and reduced immune activation. The results of the Gutsy pilot study will inform for the calculation of sample size of larger definitive randomized clinical trials assessing the influence of FMT on immune activation in PWH.

**Trial registration:**

ClinicalTrials.gov NCT06022406. Registered on 2024-08-01. https://clinicaltrials.gov/study/NCT06022406?cond=HIV&term=Gutsy&rank=1.

**Supplementary Information:**

The online version contains supplementary material available at 10.1186/s13063-025-09345-0.

### Introduction

#### Background and rationale {6a}

Antiretroviral therapy (ART) decreases human immunodeficiency virus (HIV) plasma viral load below the limit of detection, leading to major improvements in the health of people with HIV (PWH). However, the risk of developing inflammatory non-AIDS comorbidities such as cardiovascular diseases, fatty liver, neurocognition dysfunction, and cancer remains [1]. Factors associated with immune activation on ART include spontaneous cellular release of HIV RNA and proteins, cytomegalovirus (CMV) co-infection, and gut permeability allowing microbial translocation [2–5].

In PWH, an imbalanced gut microbiota composition is associated with gut epithelial damage, facilitating the translocation of bacterial and fungal products into the mucosa and bloodstream [6–9]. As it induces immune activation, microbial translocation has been linked with the development of non-AIDS comorbidities [4, 9–11]. Long-term ART only partially restores gut barrier function and fails to reduce inflammation to levels observed in uninfected controls. Hence, research focusing on improving the composition of the gut microbiota and the epithelial barrier function is important.

Furthermore, persistent HIV infection of long-lived memory CD4 T-cells and macrophages also contribute to immune activation and microbial translocation, creating a vicious cycle that nurtures inflammation [5, 12]. HIV reservoir produces RNA and protein that participate in immune activation and disruption of the immune functions [13, 14]. Importantly, the size of the HIV reservoir in CD4 T cells has been linked to the nadir CD4 T cell count, current CD4 T cell count, level of immune activation, and exhaustion of CD8+ T-cells [15–17]. It remains unknown whether the reduction of systemic inflammation can lead to a decrease in the size of the HIV reservoir in PWH.

#### Gut permeability and immune activation

HIV infection is characterized by functional impairment and CD4 T-cell decay. HIV preferentially replicates in the Th17 CD4 T-cells from the gut, inducing cell death and mucosal damage [18, 19]. Upon epithelial gut damage, microbial products penetrate the mucosa and pass into the bloodstream.

Markers of bacterial translocation, including lipopolysaccharide (LPS), LPS binding protein (LBP), and soluble CD14 (sCD14), have been correlated with immune activation and disease progression [10, 20, 21]. While bacterial translocation is thought to be a major cause of immune activation, we have shown that circulating β-D-glucan, a marker of fungal translocation, contributes to the immune activation in an LPS-independent manner [4, 9, 22].

On ART, epithelial gut damage and microbial translocation remains, contributing to a persistent systemic immune activation. Monocytes/macrophages, dendritic cells, and natural killer (NK) cells detect microbial products in the gut and draining mesenteric lymph nodes and secrete in response pro-inflammatory cytokines like interleukin 1β (IL-1β), IL-8, and tumor necrosis factor α (TNF-α). These cytokines drive CD4 T-cell activation, leading to elevated expression of the HIV co-receptor, C-C chemokine receptor (CCR) 5, and the gut homing receptor, CCR6 [19]. CD4 T-cells expressing CCR6 a cellular marker of their TH17 function have been shown by our group to be preferentially infected [19, 23].

#### Gut microbiota, dysbiosis, and immune regulation

The gut microbiota and its metabolites play a role in obesity, diabetes, cancer, and HIV infection. Their role includes food and metabolite processing, microbial ecological regulation, and immune regulation [24, 25]. Compared to uninfected controls, PWH present with relatively decreased abundance of Firmicutes and more abundant Proteobacteria in their gut microbiota, independently of sexual practice [6, 7]. The presence of *Lactobacilli* in stool is associated with higher CD4 T-cell count and a lower level of systemic immune activation [26]. Dysbiosis, an altered gut microbial composition, combined with microbial translocation has been linked to the risk of non-AIDS events and influences CD4 T-cell recovery on ART as reported by us and others [6, 9–11, 26]. Interestingly, gut microbiota composition has been linked with the size of circulating HIV reservoir in CD4 T-cells as well as with immune function, as illustrated by different microbiota in virologic/elite controllers as compared to progressors [27].

#### Summary of previous data with fecal microbiota transplant (FMT)

In PWH, the mucosal immune system, including gut protective Th17 cells, is lost within weeks post simian immunodeficiency virus (SIV) and HIV infection, contributing to damage of the barrier integrity, microbial translocation, and systemic immune activation [28, 29]. Fecal microbiota transplantation (FMT) of a healthy donor’s microbiota allows drastic changes in gut microbiota composition and has been suggested to attenuate dysbiosis, prevent gut barrier damage, and decrease immune activation [29, 30].

In a pilot study, Hensley-McBain et al. reported that FMT significantly increases the number of peripheral Th17 and Th22 cells and reduces CD4 T-cell activation in the gut of SIV-infected macaques receiving ART [31]. Moreover, the transplant was well tolerated, and no side effects were observed [31].

A small pilot study (*n* = 8) involving ART-treated individuals who received a single fecal microbiota transplantation (FMT) from a stool bank, administered via colonoscopy, reported no serious adverse effects during the 24-week follow-up period [32]. Microbial engraftment occurred but was partial and only limited to certain bacterial taxa. The authors considered that the limited effects of FMT might be related to the single dose of FMT and the delivery route which does not modify the small intestine microbiota. In Spain, Serrano-Villar et al. reported that repeated oral low-dose FMT in capsules was one way to safely introduce fecal microbiota from healthy donors to ART-treated PWH [33]. However, the study results showed that weekly low dose of oral FMT administered over 8 weeks in PWH on ART only induced a reduction of circulating levels of the gut damage marker I-FABP, observed solely 4 weeks after initiating FMT. Using proteomics, they later found a reduction in over 45 inflammatory proteins, which was sustained up to 16 weeks after the final FMT [34]. The study also did not assess HIV reservoir size. The authors suggested a higher dose of FMT could lead to a more pronounced physiological effect [33].

In patients with metastatic malignant melanoma, [name] et al. utilized single large-dose FMT capsules prepared by [name] at Western University, London, ON, Canada. This approach was safe, well tolerated, and, for those having higher levels of microbial ingraftment, was asscociated with response to immunotherapy [35]. Based on encouraging results in oncology, we developped a similar approach to be used in PWH.

### Objectives {7}

The aim of this study is to assess the influence of large-dose FMT on gut permeability and immune activation in PWH receiving ART.

#### Primary endpoint and outcome measures

Changes in plasma levels of the robust gut permeability marker REG3α levels [36].

#### Secondary endpoint and outcome measures

Safety and tolerability of FMT measured by evaluating adverse events, hematology, and serum chemistries over the course of the study. These evaluations include HIV viral load, glucose levels, lipid profile, plasma levels of C-reactive protein (CRP), and D-dimer.Changes in plasma levels of gut permeability markers including intestinal fatty acid binding protein (I-FABP) and LPS.Changes in plasma levels of pro-inflammatory markers (1–3-β-D-glucan, IL-1β, IL-6, IL-8. IP-10, IL-17A and F, IL-22) and anti-inflammatory markers (IL-10).Changes in T and myeloid cell activation in blood. CD4 and CD8+ T cell and monocyte activation levels will be measured by the expression of CD38 and HLA-DR and T cell exhaustion by PD-1.

#### Exploratory endpoint and outcome measures

Changes in microbiota composition and diversity in stools.Changes in HIV reservoir size (proviral DNA and RNA) in blood CD4 T-cells.Engraftment by comparing the gut microbiota of donors and participants.

#### Sub-study endpoint and outcome measures

Changes in inflammatory cytokines as well as T and myeloid cell activation in colon biopsies.Changes in HIV reservoir size in colon CD4 T-cells.

### Trial design {8}

Trial CTN PT038 is an exploratory single-blind, randomized at a 1:1 ratio, placebo-controlled clinical trial to assess the influence of FMT on microbial translocation, immune activation, and HIV reservoir in PWH on ART.

## Methods: participants, interventions, and outcomes

### Study setting {9}

The Gutsy study is a single-site, academic hospital-based clinical trial. All study activities are being conducted at Chronic Viral Illness Service (CVIS), McGill University Health Centre—Glen Site, Montreal, Quebec, Canada.

This academic medical center provides comprehensive care to more than 2000 PWH, offering a robust infrastructure for participant recruitment and study execution.

### Eligibility criteria {10}

#### Inclusion criteria

Participants are eligible for the study if they meet the following inclusion criteria:Male or female adults ≥ 18 years of age.Documented HIV-1 infection by western blot, enzyme immunoassay (EIA), or viral load assay.On ART for at least 3 years, and stable ART regimen (same prescription) for at least 3 months.Undetectable viral load < 50 copies/mL for the past 3 years. Viral blips below 200 copies/mL are allowed if preceded and followed by a HIV viremia below 50 copies/mL.CD4 count greater than 200 cells/µL and a CD4/CD8 ratio below 1 to select people with higher risks of inflammatory non-AIDS comorbidities and dysbiosis.Able to communicate adequately in either French or English.Able and willing to provide written informed consent prior to screening.Women of childbearing potential must have a negative serum pregnancy test at screening.Women of childbearing potential must agree to use one of the study-approved methods of birth control while in the study and until 2 weeks after completion of the study.Women of non-childbearing potential as defined as either post-menopausal (12 months of spontaneous amenorrhea and ≥45 years of age) or physically incapable of becoming pregnant with documented tubal ligation, hysterectomy, or bilateral oophorectomy.Sexually active men with a female partner of childbearing potential must agree to one of the study-approved methods of birth control until 2 weeks after study completion.

#### Exclusion criteria

Participants are not eligible to participate in the study if they meet any of the following exclusion criteria:Known allergy/hypersensitivity to polyethylene glycol.Current AIDS-related event or serious health condition including systemic infections in the last 3 months.Severe systemic diseases (e.g., uncontrolled hypertension, chronic renal failure) or active uncontrolled infections.Co-infection with active hepatitis B or C virus.Current use or have used in the past 3 months: immune-modulatory agents, antibiotics, or morphine as these drugs modulate gut microbiota.Diagnosis of diabetes mellitus (HbA1c ≥ 6.5%) as defined by the Canadian Clinical Practice Guidelines for the Prevention and Management of Diabetes.Recent changes in dietary habits, intermittent fasting, chronic constipation, or laxative use as these can affect gut microbiota composition.Psychiatric or cognitive disturbance or any illness that could preclude compliance with the study.Current participation in an experimental therapy study or receipt of experimental therapy within the last 6 months.Women who are planning to become or who are pregnant, or breast-feeding.A score of higher than 8 on the Alcohol Use Disorders Identification Test (AUDIT) questionnaire at the screening visit, suggesting an alcohol abuse problem [37, 38].

### Who will take informed consent? {26a}

Study staff under the supervision of the qualified investigator ([name]) will be responsible for obtaining informed consent from potential participants. Consent will be obtained during the screening visit (visit 1). Study staff will explain the study procedures, risks, and benefits in either French or English. The main study consent form will be reviewed with the participant. If the participant agrees, they will be asked to sign the informed consent document before any study procedures begin. As for the optional sub-study (colon mucosal biopsies), a separate informed consent form will be explained and must be signed by participants who wish to join this part of the study. Participants must first consent to the main study before being offered the optional sub-study.

### Additional consent provisions for collection and use of participant data and biological specimens {26b}

Participants are informed that stored research specimens may be used for future testing, should new markers or technologies become available. Any unforeseen or additional tests aligned with the study’s purpose (e.g., new methods for assessing gut health or HIV reservoirs) may be conducted on these samples. These future uses are covered under the initial informed consent, which specifies the scope of potential analyses.

## Interventions

### Explanation for the choice of comparators {6b}

The inclusion of a placebo group is essential to establish rigorous control. This control group allows for the evaluation of the true effect of FMT on gut permeability, immune activation, and HIV reservoir size, thereby minimizing any potential bias. By comparing the results of the FMT group with the placebo group, the specific impact of the treatment is determined more accurately.

The integrity of the blinding is ensured by making the placebo capsules identical in appearance and weight to the FMT capsules. This physical similarity is crucial so that participants cannot distinguish between the active treatment and the placebo, thus avoiding any subjective influence on their responses.

The choice of a placebo comparator is based on the need to isolate the effects of the FMT and control for the placebo effect, especially considering the subjective nature of some outcome measures, such as gastrointestinal symptoms. Microcrystalline cellulose is specifically selected because it is an inert substance that does not interact with the gut microbiota or the immune system. This ensures that any changes observed in the FMT group can be attributed to the treatment itself, and not to the substance used in the placebo.

### Intervention description {11a}

Participants are asked to continue using their typical diet throughout the study. At a first baseline visit, blood and stools are collected. Study participants then undergo a polyethylene glycol-based and electrolyte bowel cleanse the day before baseline 2 visit and then receive two doses of FMT or placebo taken orally in capsules 22 days apart. Follow-up visits are scheduled post-intervention 3 and 9 weeks after FMT/placebo treatment (see schedule of events (Fig. 1) and Supplementary Table 1 describing the schedule of events).

**Fig. 1 Fig1:**
[figure not shown]
Flow chart. Visit 1, the screening visit, will take place up to 7 weeks prior to the baseline 1 visit (day −14 ± 7 days, visit 2). At the screening visit, the informed consent document will be explained to the participant and will be signed prior to any screening and study activities. Two baseline visits will be conducted, at day −14 and day 0. All study visits will be relative to baseline 2 (day 0, visit 3). Data collected at these two baseline visits will be directly compared to determine intra-patient variability. A bowel cleanse will be given to participants prior to the treatment visit (visit 3). After the collection of blood and stool samples, two FMT treatment or placebo (30 to 40 capsules each) will be given to participants at day 0 (visit 3) and day 22 (visit 4). Blood and stool will be collected post-treatment at week 6 and week 12 (visit 5 and visit 6). Schedule of events is described in Supplementary Table 1. *Optional gut biopsies will be taken for the sub-study at the indicated time points. The consent form for the optional gut biopsy will also be explained at the screening visit, but consent for this will not be necessary to be part of the main study. Randomization will be conducted after screening one eligibility is confirmed to allow time to recruit stool donors and prepare FMT capsules for those in the FMT arm

In an optional sub-study evaluating gut mucosa architecture, immune activation, and reservoir size in the gut, colon biopsies are collected before the first dose (baseline 2) and at the end of the study, 9 weeks after the 2nd dose of FMT or placebo (week 12).

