### Sample size {14}

A total of 20 PWH participants will be enrolled, randomized 1:1 into two groups: FMT group (10 participants) and placebo group (10 participants).

The influence of gut microbiota targeting therapies on REG3α levels has not been tested yet. Hence, we calculated that based on the difference in REG3α levels between ART-treated (2441 ± 630 pg/mL) and HIV-negative controls (715 ± 243 pg/mL) [36], a sample size of 5 participants per group would allow 80% power to observe an effect, with a *p* value of 5% (https://clincalc.com/stats/samplesize.aspx). The clinical assumption and hypothesis is that complete change in the gut microbiota towards the one of HIV-negative controls would lower REG3α levels to those of controls. However, as previous FMT trials did not obtain 100% engraftment of the donor microbiota, sample size per group was doubled with 10 participants per arm. Due to the exploratory nature of the study, the small sample size is considered sufficient to detect preliminary signals in biomarkers of gut permeability, immune activation, and microbial translocation. Our study will inform larger, future randomized controlled trials as the variability in outcomes like REG3α, inflammatory markers, and microbiota composition will be estimated to support future power calculations.

As for the sub-study sample size, the optional colon biopsy sub-study includes a subset of the main study participants. No specific target number for this subgroup is defined, but participants must first qualify for and consent to the main study. In previous trials, around 50% of participants agreed to partake in the sub-study with colonoscopy as it can benefit participant with cancer screening [44–46].

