## Discussion

The Gutsy study (CTNPT 038) presents a novel and complex clinical trial evaluating the impact of FMT on immune activation in ART-treated PWH with low CD4/CD8 ratios. Several operational and practical considerations are important to highlight:Recruitment challenges: The study targets a very specific population of PWH (on stable ART for ≥3 years, CD4/CD8 ratio < 1), which may limit recruitment speed. Engagement with HIV clinics and community groups and presentations at HIV conferences are strategies proposed to address this challenge.FMT logistics: The use of encapsulated FMT introduces specific challenges: production, shipping under temperature control, storage at −80 °C, and direct observation of ingestion. Capsules are produced at a single site (St. Joseph’s Health Care, London, ON) and require coordination for timely delivery to the MUHC site.Blinding and randomization: The single-blind design, with randomization via sealed envelopes and varying capsule counts (30–40), may complicate implementation and require careful standard operating procedures to prevent unblinding.Optional colon biopsy sub-study: The invasive nature of colon biopsies may limit uptake for the sub-study. Operationally, this requires coordination with gastroenterology services, room scheduling, bowel preparation support, and post-procedure monitoring. Biopsy handling also demands careful processing, freezing or fixing, and coordination between multiple labs. However, this procedure may benefit participants with cancer screening procedure (44).Safety monitoring: Despite established safety in previous FMT studies, PWH represent a potentially immunocompromised population, so close monitoring is essential. A robust SAE reporting process is in place, and an independent DSMC oversees participant safety.Data management: The collection and storage of biological samples for both primary and exploratory endpoints require secure sample handling, proper biobanking, and detailed tracking systems. Data will be managed via eCRFs, and source documents will be retained per regulatory standards.Post-trial access and follow-up: The investigational product (FMT capsules) will not be provided after the trial. Participants will be informed of study findings but will not have continued access to treatment based on the investigational nature of the intervention.Regulatory and ethical oversight: All amendments and unexpected issues must be approved by the REB and sponsor investigator. Given the novel use of FMT in PWH, ongoing compliance with Health Canada and ICH-GCP is critical.

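### Baseline 2 is sampled the day after a bowel cleanse, so its difference from baseline 1 is not intra-patient variability, and using both visits as the pre-intervention value exposes within-arm and stool changes to a cleanse effect

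*Protocol article*

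**What the plan says.** **Timing.** The Fig. 1 legend states: "Two baseline visits will be conducted, at day −14 and day 0". Intervention description {11a} places a "polyethylene glycol-based and electrolyte bowel cleanse the day before baseline 2 visit", after the baseline 1 blood and stool have been collected. The abstract's Methods give the sampling times as "before bowel cleanse (baseline 1), before the first (baseline 2) and the 2nd (visit 4) FMT/placebo". Only baseline 1 therefore precedes the cleanse. Baseline 2 blood and stool are collected after it and before the first dose.

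**Use of the two visits.** The Fig. 1 legend says: "Data collected at these two baseline visits will be directly compared to determine intra-patient variability". Table 1 gives the baseline of the primary outcome as visits 2 and 3. Statistical methods {20a} define the pre-intervention side of the within-subject REG3α comparison as baselines 1 and 2, and plan paired t-tests or Wilcoxon signed-rank tests within each group. Stool is collected at both visits (section {33}).

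**The protocol's view of laxatives.** The exclusion criteria and section {11d} bar laxative use, along with dietary change and constipation, because these can alter the gut microbiota. Section {11d} adds that they can disturb the outcomes.

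**Purpose.** Sample size {14} says that "the variability in outcomes like REG3α, inflammatory markers, and microbiota composition will be estimated to support future power calculations".

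**The concern.** A planned intervention on the gut falls between the two measurements that the legend compares to obtain intra-patient variability. The protocol treats laxatives as a threat to its outcomes, yet it gives a purgative the day before one of its two baselines and then interprets the difference as natural fluctuation. Nothing in the article separates the two components or names baseline 1 as the reference.

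Two results are at stake. The first is the intra-patient variability figure itself. The second is any comparison within one arm: the paired pre/post tests, and the descriptive change in stool composition. If baseline 2 forms part of the starting point, some of the apparent change may be recovery from the cleanse.

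**Working it through.** The article states no figure for this point, so there is none to reproduce. The check shows what follows from the stated timing.

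**Inputs.** There are 10 participants per arm (Sample size {14}) and tests are two-sided at 5% (Statistical methods {20a}). Baseline 1 is before the cleanse and baseline 2 is the day after it. The article gives no cleanse effect on REG3α or any other marker, so three assumptions are made, in units of the within-person SD (s = 1):
- the cleanse shifts baseline 2 by a mean of m, with m from 0 to 2;
- the shift varies between people with SD t, with t from 0 to 1;
- the shift has gone by week 6.

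**1. Variability from the baseline pair.** Let D = baseline 2 − baseline 1.
- Root-mean-square form: E[D²]/2 = s² + (m² + t²)/2.
- SD-of-differences form: Var(D)/2 = s² + t²/2.

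| Assumption | Apparent SD ÷ true SD, root mean square | Apparent SD ÷ true SD, SD of differences |
|---|---|---|
| m = 0.5, t = 0 | √1.125 = 1.06 | 1.00 |
| m = 1, t = 0 | √1.5 = 1.22 | 1.00 |
| m = 2, t = 0 | √3 = 1.73 | 1.00 |
| m = 0, t = 0.5 | √1.125 = 1.06 | 1.06 |
| m = 0, t = 1 | √1.5 = 1.22 | 1.22 |

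A shift common to everyone inflates only the first form. A response that differs between people inflates both.

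**2. Within-arm paired test, no FMT effect, t = 0.** The post value is the mean of weeks 6 and 12 (variance 1/2).
- Averaged baselines: the pre value has variance 1/2, so the change has SD √(1/2 + 1/2) = 1 and bias of size m/2. The noncentrality is (m/2)·√10. At m = 1 it is 1.58.
- Baseline 2 alone: the change has SD √(1 + 1/2) = 1.22 and bias of size m. The noncentrality is m·√10/1.22. At m = 1 it is 2.58.

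With a two-sided t-test on 9 degrees of freedom:

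| m | Averaged baselines | Baseline 2 alone |
|---|---|---|
| 0 | 5.0% | 5.0% |
| 0.25 | 6.5% | 8.9% |
| 0.5 | 10.9% | 21.2% |
| 1 | 29.3% | 63.4% |
| 2 | 80.3% | 99.5% |

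With baseline 1 alone as the reference the bias is 0 and the rate returns to 5%.

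**3. Between-arm test of change.** This was simulated with 40,000 trials of 10 per arm, averaged baselines and no FMT effect. For (m, t) = (0, 0), (1, 0), (1, 0.5) and (2, 1) the type I error was 5.1%, 4.9%, 5.0% and 5.0%, and the mean difference between arms was about 0. The shared shift cancels. A variable cleanse response costs only precision: the variance of change becomes 1 + t²/4, so at t = 1 its SD is √1.25 = 1.12 times as large.

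**The case against.** The strongest reply is that the trial's conclusion rests on FMT against placebo. Both arms are cleansed, and Table 1 defines nearly every outcome, microbiota change included, as a comparison between arms. That stands. A reader might infer that the microbiota results as a whole are biased, but the article does not support this. Only within-arm and descriptive change is exposed.

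Several other limits also stand.
- The article does not say that the two baselines are averaged. It leaves variable definitions to the SAP, which is not shown. The averaged-baseline figures are one reading of the text. Using baseline 2 alone would be worse, and baseline 1 alone would remove the problem.
- A reader might infer that the variability estimates promised for future power calculations will be wrong. Sample size {14} does not say they come from the baseline pair, and a future two-arm trial can take the SD of the endpoint, or of its change, from the arms directly.
- A reader might take a 50% inflation of within-person variance as the expected size. It needs an assumed shift of one within-person SD and the root-mean-square form. With the SD of differences, a uniform shift drops out.
- The Discussion lists "room scheduling, bowel preparation support, and post-procedure monitoring" among the needs of the biopsy sub-study, and biopsies are also taken at visit 6. A reader might infer that many week-12 samples follow a second preparation and that unequal uptake distorts the week-12 contrast. The text does not name visit 6 in this connection or give the order of preparation and sampling. Chance imbalance in uptake is not bias, and section {20b} already lists sub-study participation as a subgroup.

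The reply does not rescue the Fig. 1 legend. That is a stated interpretation of a stated comparison, not a detail left to the SAP, and the cleanse makes it untenable.

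**Conclusion.** The point holds for the legend's interpretation and for within-arm results. Baseline 2 minus baseline 1 is natural variation plus any cleanse effect, and the pair alone cannot separate them. If both baselines are averaged as the pre-intervention value, a transient shift of 0, 0.5 or 1 within-person SD takes the within-arm false-positive rate from 5% to about 11% or 29%.

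These rates depend on the assumed shift, on averaging, and on the effect having gone by week 6. The shift in plasma REG3α is unknown and could be nil. For stool, the protocol's own restrictions on laxatives give reason to expect one. The randomized comparison of change is not biased, so this should be corrected but does not threaten the trial's main contrast.

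**What to change.** 1. Reword the Fig. 1 interpretation, and carry it into the SAP: report baseline 2 minus baseline 1 as cleanse effect plus natural variation.
2. Name pre-cleanse baseline 1 as the reference for the within-arm pre/post tests and for stool change, with baseline 2 as a sensitivity analysis.
3. Estimate within-person variability from samples not taken just after a bowel preparation, for example baseline 1 and week 6 in the placebo arm. Add week 12 only where no biopsy preparation preceded sampling, and flag any week-12 sample that did follow one.

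**Cost.** The change is analysis wording and one flag variable, with no new samples. The article reports data collection still in progress and the SAP as due before database lock, so there is room to make it. The variability estimate would rest on at most about 10 people instead of up to 20. It would also span about 8 weeks (day −14 to week 6) rather than 2, and it still assumes that the cleanse effect has gone by week 6. Using one baseline instead of the mean of two raises the SD of within-arm change from 1.00 to √1.5 = 1.22 within-person SDs.
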